**9.1.2 Non-measurable disease**

All other lesions (or sites of disease), including small lesions (longest diameter <20 mm with conventional techniques or <10 mm using spiral CT scan), are considered non-measurable disease. Bone lesions, leptomeningeal disease, ascites, pleural/pericardial effusions, lymphangitis cutis/pulmonis, inflammatory breast disease, abdominal masses (not followed by CT or MRI), and cystic lesions are all non-measurable.

**9.1.3 Target lesions**

All measurable lesions up to a maximum of five lesions per organ and 10 lesions in total representative of all involved organs should be identified as **target lesions** and recorded and measured at baseline. Target lesions should be selected on the basis of their size (lesions with the longest diameter) and their suitability for accurate repeated measurements (either by imaging techniques or clinically). A sum of the longest diameter (LD) for all target lesions will be calculated and reported as the baseline sum LD. The baseline sum LD will be used as reference by which to characterize the objective tumor response.

**9.1.4 Non-target lesions**

All other lesions (or sites of disease) should be identified as **non-target lesions** and should also be recorded at baseline. Non-target lesions include measurable lesions that exceed the maximum numbers per organ or total of all involved organs as well as non-measurable lesions. Measurements of these lesions are not required, but the presence or absence of each should be noted throughout follow-up.

**9.2 Guidelines for Evaluation of Measurable Disease**

All measurements should be taken and recorded in metric notation using a ruler or calipers. All baseline evaluations should be performed as closely as possible to the beginning of treatment and never more than 4 weeks before the beginning of the treatment.

The same method of assessment and the same technique should be used to characterize each identified and reported lesion at baseline and during follow-up. Imaging-based evaluation is preferred to evaluation by clinical examination when both methods have been used to assess the antitumor effect of a treatment.

**9.3** **Response Criteria**

**9.3.1 Evaluation of target lesions**

Complete Response (CR)

Disappearance of all target lesions

Partial Response (PR)

At least a 30% decrease in the sum of the longest diameter (LD) of target lesions, taking as reference the baseline sum LD

Progressive Disease (PD)

At least a 20% increase in the sum of the LD of target lesions, taking as reference the smallest sum LD recorded since the treatment started or the appearance of one or more new lesions

Stable Disease (SD)

Neither sufficient shrinkage to qualify for PR nor sufficient increase to qualify for PD, taking as reference the smallest sum LD since the treatment started

**9.3.2 Evaluation of non-target lesions**

Complete Response (CR)

Disappearance of all non-target lesions and normalization of tumor marker level

Note: If tumor markers are initially above the upper normal limit, they must normalize for a patient to be considered in complete clinical response.

Incomplete Response/Stable Disease (SD)

Persistence of one or more non-target lesion(s) and/or maintenance of tumor marker level above the normal limits

Progressive Disease (PD)

Appearance of one or more new lesions and/or unequivocal progression of existing non-target lesions

Although a clear progression of “non-target” lesions only is exceptional, in such circumstances the opinion of the treating physician should prevail, and the progression status should be confirmed at a later time by the review panel (or study chair).

**9.3.3 Evaluation of best overall response**

The best overall response is the best response recorded from the start of the treatment until disease progression/recurrence (taking as reference for progressive disease the smallest measurements recorded since the treatment started). The patient's best response assignment will depend on the achievement of both measurement and confirmation criteria (see section 9.3.1).

| Target Lesions | Non-Target Lesions | New Lesions | Overall Response |
| --- | --- | --- | --- |
| CR | CR | No | CR |
| CR | Incomplete response/SD | No | PR |
| PR | Non-PD | No | PR |
| SD | Non-PD | No | SD |
| PD | Any | Yes or No | PD |
| Any | PD | Yes or No | PD |
| Any | Any | Yes | PD |

**Note:**

- Patients with a global deterioration of health status requiring discontinuation of treatment without objective evidence of disease progression at that time should be classified as having “symptomatic deterioration.” Every effort should be made to document the objective progression, even after discontinuation of treatment.
- In some circumstances, it may be difficult to distinguish residual disease from normal tissue. When the evaluation of complete response depends on this determination, it is recommended that the residual lesion be investigated (fine needle aspirate/biopsy) before confirming the complete response status.

**9.4 Confirmatory Measurement / Duration of Response**

**9.4.1 Confirmation**

To be assigned a status of PR or CR, changes in tumor measurements must be confirmed by repeat assessments that should be performed no less than 4 weeksafter the criteria for response are first met. In the case of SD, follow-up measurements must have met the SD criteria at least once after study entry at a minimum interval of 6 weeks (see section 9.3.3). Assessments are made every 56 days.

**9.4.2 Duration of overall response**

The duration of overall response is measured from the time measurement criteria are met for CR or PR (whichever is first recorded) until the first date that recurrent or progressive disease is objectively documented (taking as reference for progressive disease the smallest measurements recorded since the treatment started).

The duration of overall CR is measured from the time measurement criteria are first met for CR until the first date that recurrent disease is objectively documented.

**9.4.3 Duration of stable disease**

Stable disease is measured from the start of the treatment until the criteria for progression are met, taking as reference the smallest measurements recorded since the treatment started.

**9.5 Time to Progression**

Time to progression is defined as the time from the first day of treatment with BAY until the first documentation of disease progression.

**9.6**  **Response Review**

All responses will be reviewed by an expert(s) independent of the study at the study’s completion. Simultaneous review of the patients’ files and radiological images will be performed.

**10. REGULATORY AND REPORTING REQUIREMENTS**

- 1. **Patient Registration**

Prior to registration, each Participating Institution must forward a copy of its IRB approval and approved consent form to the Coordinating Center (Montefiore Medical Center). The Coordinating Center will send IRB approvals to the NCI Protocol Information Office (see Multicenter Guidelines, section 10.4).

To register a patient, a completed enrollment form, eligibility checklist and signed consent form should be sent to the Coordinating Office (Montefiore Hospital). These forms may be faxed to [name] at the Coordinating Center [contact]

Following central eligibility verification, registration will be confirmed by allocation of a patient identification number.

**10.2 Adverse Event Reporting**

- - 1. **Common Toxicity Criteria**

Adverse events (AE) will use the descriptions and grading scales found in the revised NCI Common Terminology Criteria for Adverse Events (CTCAE). This study will utilize the CTCEA version 3.0 for adverse event reporting. All appropriate treatment areas should have access to a copy of the CTCAE version 3.0, which is available at <http://ctep.info.nih.gov/CTC3/>.

- - 1. **Expedited Reporting Guidelines**

**EXPEDITED ADVERSE EVENT REPORTING**

**PHASE II AND III STUDIES WITH INVESTIGATIONAL AGENTS**

**SUPPLIED UNDER CTEP-SPONSORED IND’S**

**Phase 2 and 3 Trials Utilizing an Agent under a CTEP IND: AdEERS Reporting Requirements for Adverse Events That Occur Within 30 Days1 of the Last Dose of the Investigational Agent**

|  | **Grade 1** | **Grade 2** | **Grade 2** | **Grade 3** | | **Grade 3** | | **Grades**  **4 & 52** | **Grades**  **4 & 52** |
| --- | --- | --- | --- | --- | --- | --- | --- | --- | --- |
| **Unexpected**  **and Expected** | **Unex-pected** | **Expected** | **Unexpected** | | **Expected** | | **Unex-**  **pected** | **Expected** |
| **with**  **Hospitali-zation** | **without Hospitali- zation** | **with**  **Hospitali-**  **zation** | **without Hospitali-**  **zation** |
| **Unrelated**  **Unlikely** | Not  Required | Not  Required | Not  Required | 10 Calendar  Days | Not  Required | 10 Calendar  Days | Not  Required | 10  Calendar  Days | 10  Calendar  Days |
| **Possible**  **Probable**  **Definite** | Not  Required | 10 Calendar  Days | Not  Required | 10 Calendar  Days | 10 Calendar  Days | 10 Calendar  Days | Not  Required | 24-Hour;  5 Calendar  Days | 10  Calendar  Days |
| **1 Adverse events with attribution of possible, probable, or definite that occur greater than 30 days after the last dose of treatment with an agent under a CTEP IND require reporting as follows:**  AdEERS 24-hour notification followed by complete report within 5 calendar days for:   - Grade 4 and Grade 5 unexpected events   AdEERS 10 calendar day report:   - Grade 3 unexpected events with hospitalization or prolongation of hospitalization - Grade 5 expected events   2 Although an AdEERS 24-hour notification is not required for death clearly related to progressive disease, a full report is required as outlined in the table.  December 15, 2004 | | | | | | | | | |

**Note:  All deaths on study require both routine and expedited reporting regardless of causality.  Attribution to treatment or other cause must be provided.**

- Expedited AE reporting timelines defined:
  - - “24 hours; 5 calendar days” – The investigator must initially report the AE via AdEERS within 24 hours of learning of the event followed by a complete AdEERS report within 5 calendar days of the initial 24-hour report.
    - “10 calendar days” - A complete AdEERS report on the AE must be submitted within 10 calendar days of the investigator learning of the event.
- Any medical event equivalent to CTCAE grade 3, 4, or 5 that precipitates hospitalization (or prolongation of existing hospitalization) must be reported regardless of attribution and designation as expected or unexpected with the exception of any events identified as protocol-specific expedited adverse event reporting exclusions.
- Any event that results in persistent or significant disabilities/incapacities, congenital anomalies, or birth defects must be reported via AdEERS if the event occurs following treatment with an agent under a CTEP IND.
- Use the NCI protocol number and the protocol-specific patient ID provided during trial registration on all reports.

A table showing the expected adverse events associated with BMS 247550 can be found in section 5.1 and in Appendix A.

- Telephone reports to the Investigational Drug Branch at [name] available 24 hours daily (recorder between 5pm and 9am EST).
- Expedited reports are to be submitted using AdEERS or the paper templates available at [http://ctep.info.nih.gov](http://ctep.info.nih.gov/). The NCI guidelines for expedited adverse event reporting are also available at this site.
- A list of agent specific expected adverse events (ASAEL) can be found in this protocol.

**10.2.3 Forms**

AE’s should be reported electronically using the AdEERS system, full details of which are available at <http://ctep.info.nih.gov/AdEERS/>.

If electronic reporting is not possible within the required timeframe, reports should be made on the DCTD Form for Reporting AEs Occurring with Investigational Agents Obtained from the NCI. This form can be downloaded from the CTEP home page <http://ctep.info.nih.gov/InfoForms/default.htm>. Cases of secondary AML/MDS are to be reported using the NCI/CTEP Secondary AML/MDS Report Form.

**10.3 Data Reporting**

Data will be reported electronically to the Coordinating Center, using an Excel spreadsheet template that will be provided to the Participating Institutions.

Data updates should be forwarded to the Coordinating Center within 2 weeks of completion of each treatment cycle.

This study will be monitored by the Clinical Data Update System (CDUS) version 2.0. Cumulative CDUS data will be submitted electronically to CTEP by the Coordinating Center on a quarterly basis. Reports are due January 31, April 30, July 31, and October 31. Instructions for submitting data using the CDUS can be found on the CTEP home page (<http://ctep.info.nih.gov/CtepInformatics/CDUS/Default.htm>). Sample data collection forms are contained in Appendix G.

**10.4 CTEP Multicenter Guidelines**

**10.4.1 Responsibilities of the Protocol Chair**

- The Protocol Chair will be the single liaison with the CTEP Protocol and Information Office (PIO). The Protocol Chair is responsible for the coordination, development, submission, and approval of the protocol as well as its subsequent amendments. The protocol must not be rewritten or modified by anyone other than the Protocol Chair. There will be only one version of the protocol, and each Participating Institution will use that document. The Protocol Chair is responsible for assuring that all Participating Institutions are using the correct version of the protocol.
- The Protocol Chair is responsible for the overall conduct of the study at all Participating Institutions and for monitoring its progress. All reporting requirements to CTEP are the responsibility of the Protocol Chair.
- The Protocol Chair is responsible for the timely review of Adverse Events (AE) to assure safety of the patients.
- The Protocol Chair will be responsible for the review of and timely submission of data for study analysis.

**10.4.2 Responsibilities of the Coordinating Center**

- Each Participating Institution will have an appropriate assurance on file with the Office for Protection from Research Risks (OPRR), NIH.The Coordinating Center is responsible for assuring that each Participating Institution has an OPRR assurance and must maintain copies of IRB approvals from each participating site.
- Prior to the activation of the protocol at each Participating Institution, an OPRR form 310 (documentation of IRB approval) must be submitted to the CTEP PIO.
- The Coordinating Center is responsible for central patient registration. The Coordinating Center is responsible for assuring that IRB approval has been obtained at each participating site prior to the first patient registration from that site.
- The Coordinating Center is responsible for the preparation of all submitted data for review by the Protocol Chair.
- The Coordinating Center will maintain documentation of AE reports. There are two options for AE reporting: (1) Participating Institutions may report directly to CTEP with a copy to the Coordinating Center, or (2) Participating Institutions report to the Coordinating Center who in turn report to CTEP. The Coordinating Center will submit AE reports to the Protocol Chair for timely review.
- Audits may be accomplished in two ways: (1) source documents and research records for selected patients are brought from participating sites to the Coordinating Center for NCI audit , and (2) selected patient records will be audited on-site at participating sites yearly. The NCI will be perform all audits at the Coordinating Center, subsequently the Coordinating Center will be responsible for having all source documents, research records, all IRB approval documents, NCI Drug Accountability Record forms, patient registration lists, response assessments scans, x-rays, etc. available for the audit.

**10.5 Clinical Trials Agreement (CTA)**

The agent, BAY 43-9006, used in this protocol is provided to the NCI under a Clinical Trials Agreement (CTA) between Bayer Pharmaceuticals [hereinafter referred to as “Collaborator”] and the NCI Division of Cancer Treatment and Diagnosis. Therefore, the following obligations/guidelines, in addition to the provisions in the “Intellectual Property Option to Collaborator” terms of award modifications, apply to the use of BAY 43-9006 in this study:

1. BAY 43-9006 may not be used for any purpose outside the scope of this protocol, nor can BAY 43-9006 be transferred or licensed to any party not participating in the clinical study. Collaborator data for BAY 43-9006 are confidential and proprietary to Collaborator and shall be maintained as such by the investigators.

2. For a clinical protocol where there is an investigational agent used in combination with (an)other investigational agent(s), each the subject of different CTAs, the access to and use of data by each Collaborator shall be as follows (data pertaining to such combination use shall hereinafter be referred to as "Multi-Party Data”.):

a. NCI must provide all Collaborators with prior written notice regarding the existence and nature of any agreements governing their collaboration with NIH, the design of the proposed combination protocol, and the existence of any obligations which would tend to restrict NCI's participation in the proposed combination protocol.

b. Each Collaborator shall agree to permit use of the Multi-Party Data from the clinical trial by any other Collaborator solely to the extent necessary to allow said other Collaborator to develop, obtain regulatory approval, or commercialize its own investigational agent.

c. Any Collaborator having the right to use the Multi-Party Data from these trials must agree in writing prior to the commencement of the trials that it will use the Multi-Party Data solely for development, regulatory approval, and commercialization of its own investigational agent.

3. Clinical Trial Data and Results and Raw Data developed under a CTA will be made available exclusively to Collaborator, the NCI, and the FDA, as appropriate.

4. When a Collaborator wishes to initiate a data request, the request should first be sent to the NCI, who will then notify the appropriate investigators (Group Chair for Cooperative Group studies, or PI for other studies) of Collaborator's wish to contact them.

5. Any data provided to Collaborator for Phase 3 studies must be in accordance with the guidelines and policies of the responsible Data Monitoring Committee (DMC), if there is a DMC for this clinical trial.

1. Any manuscripts reporting the results of this clinical trial should be provided to CTEP for immediate delivery to Collaborator for advisory review and comment prior to submission for publication. Collaborator will have 30 days from the date of receipt for review. Collaborator shall have the right to request that publication be delayed for up to an additional 30 days in order to ensure that Collaborator’s confidential and proprietary data, in addition to Collaborator’s intellectual property rights, are protected. Copies of abstracts should be provided to CTEP for forwarding to Collaborator for courtesy review as soon as possible and preferably at least three (3) days prior to submission, but in any case, prior to presentation at the meeting or publication in the proceedings. Copies of any manuscript and/or abstract should be sent to:

Regulatory Affairs Branch, CTEP, DCTD, NCI

[name]

[name]

[contact]

The Regulatory Affairs Branch will then distribute them to Collaborator. No publication, manuscript or other form of public disclosure shall contain any of Collaborator’s confidential/ proprietary information.

**11. STATISTICAL CONSIDERATIONS**

**11.1 Endpoints**

Primary endpoint:

- Response rate (RR)

Secondary endpoints:

- Time to progression (TTP)
- Toxicity
- Correlative Data
  1. **Study Design / Stratification Factors**

*Clinical Endpoints*

The primary endpoint of this trial is response rate defined as is either a complete or a partial response at the end of second cycle, using the RECIST criteria.

The response rate for standard of care DTIC is 5-10%. If the response is < 5%, the new treatment will not be considered for further study.

In each subgroup defined by BRAF status, a minimax two-stage Simon design will be used to test the null hypothesis that response rate at the end of second cycle (56 days) is p  0.05 versus the alternative that the response rate is p ≥ 0.20. If the drug is actually not effective, there is 3.3% probability of concluding that it is (the target was 5%). If the drug is actually effective there is a 14.2% probability of concluding that it is not (the target was 20%). After testing the drug on 13 patients per BRAF subgroup in the first stage, the trial will be terminated if 0 patients per subgroup respond. If the trial goes on to the second stage, a total of 37 patients per BRAF subgroup will be studied. If the total number responding is less than or equal to 4 patients per subgroup, the drug is rejected for that subgroup.

The overall response rate along with subgroup-specific response rates will be estimated at the end of the trial along with 95% confidence interval.

*Correlative Study Endpoints*

An important goal of this trial is to evaluate the biological markers pre and post treatment. Eligibility for the first stage of the trial (first 13 patients in each subgroup) requires that patients have biopsiable sites of disease. Tumor tissue will be collected and assessed for change in BRAF, P-MAPK, CDK4, and Cyclin D1 levels pre versus post treatment by analyzing the changes in the intensity of the specific bands on immunoblot. This is usually done visually (increase, no change, decrease) but can be quantified using a digital scanner. It is critically important to ensure that equal amounts of protein are loaded on to each lane. This can be confirmed by comparing the intensity of the p85 PI3k bands. The proportion of patients with decreases in levels of BRAF, CDK4, or phospho-MAPK will be estimated along with 95% confidence intervals.

Cyclin D1 and phospho-MAPK expression will also be assessed by immunohistochemistry. The percentage of tumor cells staining for either marker will be quantified visually and expressed as a percentage of positively-staining tumor cells. In this study, we are measuring phospho-MAPK both by immunoblotting and by immunohistochemistry. These two techniques are complimentary in that immunoblotting measures the relative amount of phospho-MAPK in the tumor while immunohistochemistry gives information as to the percentage of cells expressing the protein.

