## 2.1.1 Standard Therapy

In the first-line chemotherapy treatment of patients with stage IV disease, agents with reproducible activity against melanoma include DTIC, cisplatin, nitrosoureas, and vinca alkaloids. DTIC is the most active single agent with response rates ranging from about 10% to 20%, and median response durations of 4 to 6 months (2). Although several recent studies using a combination of DTIC and other agents have shown higher response rates, these combinations have not proven to be superior to single agent DTIC for the general population. Similarly, a Phase III study comparing temozolomide to DTIC showed no substantial improvement in survival or in other primary clinical endpoint (3).

A variety of combination chemotherapy regimens have produced response rates of 30% to 50% in single-institution Phase 2 trials. Two of the more active regimens were the 3-drug combination of cisplatin/vinblastine/DTIC (CVD) (4) and the 4-drug combination of cisplatin/DTIC/BCNU/tamoxifen (CDBT) (5). However, in a randomized multi-institutional trial comparing CVD to DTIC alone, the CVD arm was not significantly superior in response rate, response duration, or survival (6). In a recent update of this trial that encompassed approximately 150 patients, the CVD arm produced a 19% response rate compared to 14% for DTIC alone with no difference in either response duration or survival. A randomized, Phase 3 trial (EST 91-140) also demonstrated no significant survival benefit associated with CDBT relative to DTIC alone.

Several recent studies have indicated potential value for the addition of either interferon- or tamoxifen to DTIC (7-9). The actual benefit of the addition of interferon and/or tamoxifen to DTIC in patients with advanced melanoma was tested by the Eastern Cooperative Oncology Group (ECOG) in a large-scale, four-arm, Phase 3 trial (EST 3690). The overall response rate was 18% (range 12% to 21% for the 4 arms), the median time to treatment failure was 2.6 months, and median survival was 9.1 months. There was no increase in objective response, increased duration of time to progression, or survival advantage attributable to the addition of interferon, tamoxifen, or both to DTIC. Based on this trial and the cumulative data from prior studies, there is no compelling evidence to support the addition of either interferon or tamoxifen to DTIC in this disease.

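### Section 11.2 puts the DTIC response rate at 5-10%, section 2.1.1 at about 10-20%; the 3.3% false-positive rate gives no protection against advancing a drug no better than DTIC

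*Protocol*

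**What the plan says.** Section 11.2 (Study Design / Stratification Factors, clinical endpoints) gives one external benchmark: "The response rate for standard of care DTIC is 5-10" per cent. The next sentence sets the cut-off: "If the response is < 5%, the new treatment will not be considered for further study". The following paragraph turns this into a test in each BRAF subgroup: "a minimax two-stage Simon design will be used to test the null hypothesis that response rate at the end of second cycle (56 days) is" at most 0.05, "versus the alternative that the response rate is p ≥ 0.20". For an ineffective drug, "there is 3.3% probability of concluding that it is (the target was 5" per cent); the stated type II error is 14.2%. A subgroup stops if none of the first 13 patients responds, and the drug is rejected there if 4 or fewer of 37 respond.

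Section 2.1.1 (Standard Therapy), on first-line treatment of stage IV disease, gives different DTIC rates:

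- Single agent: "DTIC is the most active single agent with response rates ranging from about 10% to 20" per cent.
- Randomised comparison with a three-drug regimen: "the CVD arm produced a 19% response rate compared to 14% for DTIC alone".
- Four-arm phase 3 trial of DTIC with or without interferon and tamoxifen: "The overall response rate was 18% (range 12% to 21% for the 4 arms").

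**The concern.** A reader of section 11.2 meets the DTIC rate, then the 5% cut-off, then the 5% null, with nothing in between. It is natural to take 5% as the low end of what standard care achieves. By section 2.1.1 it is half the low end of the DTIC range, and it lies below every DTIC figure quoted there. The smallest passing result, 5 of 37 (13.5%), falls inside the background DTIC range, and the 20% alternative is the top of that range.

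This matters because sections 3.1.3 and 3.2.1 exclude prior chemotherapy for metastatic disease, so first-line DTIC is the treatment these patients would otherwise be likely to receive. Section 2.1.3 also closes by calling for agents more active than platinum and DTIC. The response rule is the only primary go/no-go criterion in each subgroup. If its 3.3% is read as the risk of taking forward a drug no better than standard care, the reader is misled by a wide margin.

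**Working it through.** **Inputs.** All come from section 11.2 unless noted: first stage 13 patients, continue with at least 1 response; total 37 patients (24 more in stage 2), pass with at least 5 responses; null 5%, alternative 20%. DTIC rates from section 2.1.1: 10% and 20% (ends of the single-agent range) and 14% (DTIC alone, randomised trial). The 18% overall rate and the 12-21% arm range are left out because they include DTIC combinations.

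**Formula.** With X1 ~ Bin(13, p) and X2 ~ Bin(24, p) independent,

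P(pass | p) = sum over x = 1 to 13 of P(X1 = x) × P(X2 ≥ 5 − x).

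For x of 5 or more the second factor is 1.

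**Reproducing the plan's figures.** At p = 0.05:

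- x = 1: 0.3512 × 0.0298 = 0.0105
- x = 2: 0.1109 × 0.1159 = 0.0129
- x = 3: 0.0214 × 0.3392 = 0.0073
- x = 4: 0.0028 × 0.7080 = 0.0020
- x ≥ 5: 0.0003

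The unrounded total is 0.0329, the stated 3.3%. At p = 0.20 the same sum gives 0.8583, so the type II error is 0.1417, the stated 14.2%. The arithmetic in section 11.2 is right.

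**Same rule at the background DTIC rates.** Contributions by number of first-stage responders:

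| True rate | x = 1 | x = 2 | x = 3 | x = 4 | x ≥ 5 | P(pass) |
|---|---|---|---|---|---|---|
| 10% | 0.0787 | 0.1067 | 0.0706 | 0.0255 | 0.0065 | 0.2878 |
| 14% | 0.1307 | 0.1957 | 0.1508 | 0.0688 | 0.0260 | 0.5720 |
| 20% | 0.1315 | 0.2373 | 0.2376 | 0.1528 | 0.0991 | 0.8583 |

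(Totals are from unrounded terms.) A drug with a true rate equal to DTIC therefore passes in a given subgroup with probability 28.8%, 57.2% or 85.8%. The first figure is 28.8 / 3.3 = 8.7 times the printed false-positive rate. It applies even at the top of section 11.2's own 5-10% range, so the gap does not depend wholly on which DTIC range is right.

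**Evidence at the boundary.** The exact (Clopper-Pearson) 95% interval for 5 of 37 is 4.5% to 28.8%, which covers 5% and the whole 10-20% range.

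**The case against.** The strongest reply is that 5% is an activity floor. Section 11.2 never says that the null was derived from the DTIC rate. Its cut-off sentence reads as a minimum below which the drug is dropped, and 5% is only the lower end of its own DTIC range. For that null 3.3% is correct, and testing a single agent against a floor is a legitimate phase II choice. Objectives 1.1 to 1.5 plan no comparison with DTIC, and section 11.2 commits to 95% confidence intervals by subgroup, which would show how imprecise a borderline result is. All of this stands. A reader might infer that the null was computed from a wrong DTIC rate, that 3.3% is an error, or that the trial sets out to show DTIC-level activity. The documents support none of these.

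Comparability is also a fair point. The endpoint is response at 56 days, with confirmation (9.4.1) and independent review (9.6), while the background rates carry no time point or criteria. The historical rates may overstate what DTIC would score here. The protocol, however, does not use this to explain 5-10%.

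The reply does not remove the conflict between the two DTIC figures. Nor does it supply the missing statement that 5% is a floor and not the standard-of-care rate.

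**Conclusion.** The point holds as a fault in the stated benchmark and in what a pass may be taken to mean, not in the design's arithmetic. Sections 11.2 and 2.1.1 give DTIC ranges that meet only at 10%, with no reconciliation, and the lower one stands beside the decision rule. The 3.3% is right at a true rate of 5%. Against a drug that only matches DTIC, the chance of a positive subgroup is 28.8% at 10%, 57.2% at 14% and 85.8% at 20%. These figures rest on the exact 0/13, 4/37 rule, apply to one subgroup at a time, and assume that the historical DTIC rates hold for the 56-day endpoint. The protocol should be corrected, but the design can stand.

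**What to change.** In section 11.2:

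1. Bring the DTIC rate into line with section 2.1.1, or explain why a lower rate applies to this endpoint.
2. State that the 5% null is a minimum-activity floor and not the standard-of-care rate, so that passing supports only a response rate above 5%, and not activity equal to or better than DTIC.
3. Print the pass probabilities at 10%, 14% and 20% (28.8%, 57.2%, 85.8%) beside the 3.3%, with the comparability assumption.

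The cost is a few sentences and a less favourable stated operating characteristic. The decision rule, the analysis and the 37 patients per subgroup are unchanged.

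Raising the pass mark to test against a DTIC-level null is not recommended as a repair. Requiring at least 8 of 37 would bring the pass probability at 10% down to 2.7%, but power at the protocol's own 20% would fall from 85.8% to 46.2%. It would also change the decision rule in a trial that, by section 3.1.1, is already accruing.
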